7.4.3 Short Form-12

7.4.4 EQ-5D

7.4.5 Previous mental health problems (self-reported), including treatment

7.4.6 Socio-demographic measures including age, number of children at home, ethnicity, income, occupation and relationship to perpetrator

7.4.7 Cost data

- health service use of participants (self report)
- travel costs
- intervention training and delivery costs

7.4.8 Process measures

- numbers of sessions attended
- digital recording of treatment sessions with independent evaluation of intervention fidelity
- supervision sessions attended by advocates

**8. Analysis**

- Intention-to-treat and per-protocol analyses, including all randomised patients for whom outcome data are available. Analysis of covariance with the one year CORE-OM score as the dependent variable, adjusted for baseline CORE-OM score and the minimisation variables. A standardised effect size will be calculated by dividing the effect size by the SD, pooled across the 2 groups with a sensitivity analysis for the effect of missing data with conservative assumption. To assess the stability of any treatment effect we will fit a mixed model for CORE-OM scores at 4, 8, and 12 months, adjusted for baseline CORE-OM and minimisation variables, using treated number of sessions as a fixed categorical effect. Binary and continuous secondary outcome measures will be analysed with logistic regression and analysis of covariance, respectively, adjusted for baseline CORE-OM scores and minimisation variables.
- With directly collected patient and treatment costs we will calculate cost-effectiveness from NHS and societal perspectives, using EQ-5D scores to generate quality adjusted life years and expressing these findings in terms of incremental cost per QALY gained.

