**4. Objectives**

# To train eight domestic violence advocates, four at Bristol based advocacy organisation Next Link and four from Cardiff Women’s Aid to implement the intervention

4.2.1 To recruit **125** women to the intervention programme and **125** to the control arm

4.2.2 To follow up the women for 12 months from baseline measurements post-recruitment.

4.2.3 To administer baseline and 4 monthly follow up measures for 12 months from recruitment.

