6.4 Control arm

This would be normal support from advocates, varying from a single session and referral to other agencies or regular meetings over a period of months.

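### The main intention-to-treat analysis uses only women with a 12-month CORE-OM score; their 4- and 8-month scores enter only a supporting model built on sessions received, and ITT is not ranked above per-protocol

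*Protocol*

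**What the plan says.** All the relevant analysis text is in Protocol section 8.

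- **Analysis set:** "Intention-to-treat and per-protocol analyses, including all randomised patients for whom outcome data are available". Neither analysis is called primary.
- **Main model:** "Analysis of covariance with the one year CORE-OM score as the dependent variable, adjusted for baseline CORE-OM score and the minimisation variables".
- **Missing data:** one provision, "with a sensitivity analysis for the effect of missing data with conservative assumption". The assumption is not described further.
- **Interim scores:** "To assess the stability of any treatment effect we will fit a mixed model for CORE-OM scores at 4, 8, and 12 months". This model carries the same covariates as the main one, and its treatment term is described thus: "using treated number of sessions as a fixed categorical effect".

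Three other places bear on this. Section 4.2.3 sets the visit schedule ("To administer baseline and 4 monthly follow up measures for 12 months from recruitment"), so interim scores will exist for many women who miss the last visit. Section 7.4.8 lists "numbers of sessions attended" as a process measure. Section 6.4 describes control support as "varying from a single session and referral to other agencies or regular meetings over a period of months".

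**The concern.** The label intention-to-treat suggests that every randomised woman contributes. Under the rule in section 8 only those with a 12-month score do. Whether the result is unbiased then depends on loss at 12 months being unrelated to outcome once arm and baseline CORE-OM are known. What happened to a woman at 4 and 8 months is left out of that condition, although it is recorded.

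The setting makes unequal loss plausible. Women are told their arm (section 7.1.3), the outcome is self-completed (section 7.4.1), some are supported by safe-house or refuge teams (section 7.2), and control contact may be a single session (section 6.4).

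The mixed model could have met the concern, because it uses all three follow-up scores. As worded, it contrasts women by how many sessions they received, which is decided after randomisation and may reflect prognosis. With ITT and per-protocol also unranked, the protocol does not say which estimate answers the trial question.

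**Working it through.** **1. Who contributes to what (section 8)**

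| Follow-up CORE-OM available | Main ANCOVA | Mixed model |
|---|---|---|
| 4, 8 and 12 months | yes | yes |
| 4 and 8 months only | no | yes |
| 4 months only | no | yes |
| none | no | no |

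The mixed-model column assumes a standard likelihood fit to all available scores. Rows two and three are the women whose recorded follow-up does not reach the main analysis.

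**2. What the mixed model's treatment term estimates**

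If sessions means therapy sessions, every control woman has zero and shares that category with intervention women who never attended. If it also counts ordinary support meetings, categories mix the arms because control contact varies. If arm were fitted as well, its coefficient would compare arms at a fixed session count. None of these is the randomised comparison.

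**3. Does the sample size already allow for loss?**

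Inputs from section 7.4.1: 0.4 SD, 80% power, 5% significance (two-sided assumed); 1:1 allocation from section 7.2.

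n per arm = 2(1.96 + 0.84)² / 0.4² = 98 before rounding up with unrounded normal quantiles, so 99 per arm and 198 in total.

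The stated 250 is not reproduced from these inputs. It fits an unstated loss of about 20%: 198 / 0.80 = 247.5, so 248. Power with 250 randomised is 88.5% with no loss, 80.7% with 20% loss and 75.4% with 30% loss. Loss may therefore have been allowed for in power. That does nothing about bias.

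**4. Illustration of the bias**

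Assumptions, none of them from the documents: 250 women, true effect -0.40 SD, about a quarter missing at 12 months, and log-odds of loss linear in the 8-month score. Two estimators are compared: ANCOVA on women with a 12-month score, and the same contrast with missing 12-month scores predicted from baseline, 4 and 8 months. Each scenario used 3,000 simulated trials.

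Correlations 0.5 with baseline and 0.65 to 0.7 between follow-ups:

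| Loss at 12 months | Complete-case | Using interim scores |
|---|---|---|
| Unrelated to outcome | -0.40 (SD 0.125) | -0.40 (SD 0.119) |
| Depends on 8-month score alike in both arms | about -0.40 | about -0.40 |
| Opposite by arm, 0.5 per SD: distressed controls and improved intervention women leave | about -0.3 | about -0.40 |
| Opposite by arm, 0.5 per SD, directions reversed | about -0.5 | about -0.40 |
| Opposite by arm, 1.0 per SD | about -0.16 to -0.19, or -0.60 reversed | about -0.40 |

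Correlation 0.6 between all visits:

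| Loss at 12 months | Complete-case | Using interim scores |
|---|---|---|
| Alike in both arms (0.7 per SD) | -0.40 | -0.40 |
| Distressed women leave the intervention arm only (1.0 per SD) | -0.45 | -0.40 |
| Opposite by arm (-0.5 control, +1.0 intervention) | -0.48 to -0.49 | -0.40 |

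**5. Precision under unrelated loss**

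First set: 1 - (0.119 / 0.125)² = 1 - 0.906 = 9% less variance. Second set: 1 - (0.1106 / 0.1133)² = 5%. The gain depends on how closely the interim scores predict the 12-month score.

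**The case against.** **Section 8 already uses the interim scores and already addresses missing data.** Correct. A reader might infer that the 4- and 8-month scores go unused or that missing data are ignored; neither is so. The interim scores enter the mixed model, and a missing-data sensitivity analysis is planned. What remains is that they do not inform the main estimate, and the model that uses them is not specified as a comparison of arms.

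**Baseline-adjusted ANCOVA at one named time point is a standard primary analysis.** It is, and if loss is unrelated to progress or depends on it alike in both arms, the bias is about nil. The biased cases require dependence that differs by arm, and both the size and the direction follow from the assumption chosen.

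**The conservative assumption is itself at fault.** A reader might infer this because no single assumption is sure to be conservative when loss differs by arm. The figures at hand do not support it. Carrying the baseline score forward, a method the protocol never names, gave -0.31, -0.27 and -0.23 against a true -0.40, all nearer to no effect. The exact assumption can properly be left to a statistical analysis plan.

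**Planning a per-protocol analysis is not an error.** Agreed. Its definition may also stand in a plan not shown, so no attendance-bias figure can be put on it from this document. Only the absence of a ranking against ITT stands.

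**Conclusion.** The point holds in a limited form. As written, the main analysis is a 12-month complete-case ANCOVA under an ITT label, ITT is not placed above per-protocol, and no analysis described gives a contrast of randomised arms using every woman's follow-up CORE-OM.

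The size cannot be derived from the protocol, which states no dropout rate, attendance pattern or correlation between visits. With about a quarter lost, the illustration runs from no bias (loss alike in both arms) to an estimate of about -0.3 or -0.5 SD against -0.4 (opposite dependence at 0.5 log-odds per SD), and further under stronger dependence. The precision gain under unrelated loss is about 9% in variance, or about 5% with weaker correlations. It would be wrong to conclude that the trial's result will be biased, or biased towards or away from benefit. The documents support only that the plan is exposed to such bias and that data already scheduled for collection would reduce it. This should be changed because the remedy is cheap.

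**What to change.** 1. State that ITT is the primary analysis and that per-protocol, or any other adherence analysis, is secondary.
2. Take the primary 12-month contrast from the longitudinal model already planned. Use randomised arm by time in place of number of sessions, adjust for baseline CORE-OM and the stratification factors of section 7.2 (section 8 calls them minimisation variables), and include every woman with any follow-up CORE-OM. ANCOVA after multiple imputation by arm, using the 4- and 8-month scores, is an acceptable alternative.
3. Keep the complete-case ANCOVA and the planned missing-data analysis as sensitivity analyses. If the relation with sessions attended is of interest, report it separately as exploratory.

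Cost: slightly more analysis work and no new data. The result then relies on loss being at random given arm, baseline and the interim scores, which in practice asks less than the complete-case analysis does. Women with no follow-up score at all still depend on baseline information alone, so the sensitivity analyses remain necessary.

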6.3 Intervention arm

8 hour-long weekly sessions tailored to the needs of the individual woman and 1-2 booster sessions over the next 6 months. The advocates will provide time-limited interventions using a variety of (primarily) cognitive behavioural psychological techniques focussing within any one session on a specific presenting problem, such as hyper-arousal, sleeping difficulties or parenting problems. The advocate will empower the client to apply therapeutic strategies (such as diary keeping, challenging thoughts or goal setting) to promote recovery from each problem. While the intervention is manualised, each package will be tailored to promote needs-led flexibility in the problem focus and the order in which problems are addressed over an eight session contract. Common elements characterising all interventions will include a focus on domestic violence as an aetiological factor, post-traumatic stress as a framework and attention to the therapeutic alliance.

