7.2 Randomisation

Participants will be randomly allocated, in a1:1 ratio to the intervention and control arms respectively via a computer program accessed remotely by the recruiting researcher. Information about allocation will be communicated to Next Link/Cardiff Women’s Aid by the researcher recruiting. Allocation will be stratified by whether women receive support from the safe house team or resettlement team at Next Link, or the refuge team or tenant support team at Cardiff Women’s Aid.

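### The mixed model meant to show whether the treatment effect is stable names sessions attended, a post-randomisation variable, where arm-by-visit terms are needed

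*Protocol*

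**What the plan says.** Section 8 (Analysis) sets the primary analysis as "Analysis of covariance with the one year CORE-OM score as the dependent variable", with adjustment for the baseline score and the minimisation variables. It then adds a repeated-measures analysis: "To assess the stability of any treatment effect we will fit a mixed model for CORE-OM scores at 4, 8, and 12 months". That model is "adjusted for baseline CORE-OM and minimisation variables", and the sentence ends "using treated number of sessions as a fixed categorical effect". Neither visit nor an interaction of arm with visit is mentioned.

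Three other places bear on what the session variable is:

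- Section 7.4.8 lists "numbers of sessions attended" among the process measures, so it is observed after allocation.
- Section 6.3 describes the intervention as "8 hour-long weekly sessions tailored to the needs of the individual woman and 1-2 booster sessions over the next 6 months".
- For the controls, section 6.4 says: "This would be normal support from advocates, varying from a single session and referral to other agencies or regular meetings over a period of months".

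**The concern.** The stated aim and the named effect do not match. Whether an effect is stable is answered by comparing the arms at 4, 8 and 12 months and asking whether the difference changes. The count of sessions has one value per woman, so its main effect gives one contrast per attendance level, averaged over the visits.

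Attendance is also partly the woman's own doing after randomisation. Women who complete the course and women who stop may differ in prognosis, and then differences between session levels mix selection with effect.

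This is the only CORE-OM analysis named in the protocol that uses the 4- and 8-month scores. Fitted as written, it would give no randomised comparison from those visits and would not address persistence of benefit.

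**Working it through.** The protocol gives no figure that this point depends on, so the check is partly reasoning and partly illustration with assumed inputs.

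**1. Can a sessions main effect show stability?** I used 2,000 simulated trials per scenario with 250 women allocated 1:1 (sections 4.2.1 and 7.2) and three complete visits.

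Assumptions:
- The outcome has SD 1.
- An unmeasured prognosis variable has weight 0.6 in both the baseline and each follow-up score.
- There is a persistent person effect with SD 0.5.
- Controls form a zero-session category.
- Intervention women fall into three roughly equal attendance groups.

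With complete data and a random intercept, the session contrasts equal those from an ANCOVA on each woman's mean over the visits. With attendance unrelated to prognosis:

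| True effect at 4 / 8 / 12 months (SD) | Sessions model: low / middle / full vs none | Arm effect by visit |
|---|---|---|
| -0.4 / -0.4 / -0.4 | -0.40 / -0.40 / -0.41 | -0.40 / -0.40 / -0.40 |
| -0.8 / -0.4 / 0 | -0.40 / -0.40 / -0.40 | -0.80 / -0.40 / 0.00 |

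Both patterns average -0.4, since (-0.8 - 0.4 + 0)/3 = -0.4, and the sessions model returns that average in both cases. Arm effects by visit recover each pattern.

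**2. Does an implicit arm term rescue the model?** There are two readings of the count.

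*Only therapy sessions count, so controls probably have zero.* If every intervention woman attends at least once, a design with intercept, arm and three session categories has 5 columns and rank 4, so arm cannot be estimated. If m intervention women never attend, the arm coefficient rests on those m against the 125 controls. Its standard error is about sqrt(1/m + 1/125) residual SDs. The protocol gives no m, so I take a range:
- m = 5: sqrt(0.200 + 0.008) = 0.46
- m = 10: sqrt(0.100 + 0.008) = 0.33
- m = 25: sqrt(0.040 + 0.008) = 0.22
- full randomised comparison: sqrt(1/125 + 1/125) = 0.13

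That coefficient also compares self-selected never-attenders with all controls.

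*Control advocacy meetings count too.* Arm can then be estimated, but only by comparing women with the same number of quite different contacts. Groups matched on a post-randomisation count are not comparable by randomisation.

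**3. Confounding, if attendance tracks prognosis.** The documents give no correlation r between attendance and unmeasured prognosis. With no true effect, the same simulation gives:

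| Assumed r | Low / middle / full vs none (SD) |
|---|---|
| 0 | 0.00 / 0.00 / 0.00 |
| 0.3 | +0.13 / 0.00 / -0.13 |
| 0.5 | +0.22 / 0.00 / -0.21 |

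A hand check of the full-attendance value: the top group has a mean latent attendance of about 1.09 SD, so the contrast is about -0.6 x r x 1.09 x (1 - 0.36). This gives -0.13 at r = 0.3 and -0.21 at r = 0.5. Reversing the sign of r mirrors the pattern, so the bias can run either way. For scale, section 7.4.1 sizes the trial on 0.4 SD.

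**4. Timing.** Eight weekly sessions take about 2 months, and the boosters follow over 6 more, so the count may not be final until about 2 + 6 = 8 months after the first session. The 4-month CORE-OM can precede part of the attendance used to explain it.

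**The case against.** The strongest reply is that no model in section 8 names an arm term. The primary ANCOVA and the secondary-outcome models list only their adjustments and leave the group comparison understood. A reader might infer that randomised arm has been replaced by sessions, but the text does not establish that. This stands, and the point is therefore made on both readings. An implicit arm term does not repair the model, for the reasons in step 2.

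A second reply is that visit coding, the interaction and the covariance structure are normally left to the SAP. That is fair for those details, and their absence alone would be no finding. The session clause is different: the protocol positively names it for a stated aim that it does not serve.

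Third, a reader might take every control woman to have zero sessions. Section 7.4.8 does not limit the count to one arm, and section 6.4 describes control contact that could be counted. Zero is likely if only therapy sessions are meant, but it is an inference, and the aliasing result depends on it.

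Fourth, the clause reads as garbled and may be a drafting slip, or a dose analysis may have been intended. Either is possible. A slip still needs correcting, and a dose question is not the purpose the sentence gives.

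**Conclusion.** The clause is wrong as written. A main effect of sessions attended cannot show whether the arm difference persists over 4, 8 and 12 months, and conditioning on it removes the protection of randomisation. Neither conclusion needs any assumption about the link between attendance and prognosis.

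Confounding of the session contrasts is a further, conditional problem. It is zero if attendance is unrelated to prognosis and can go in either direction otherwise. The 0.13 to 0.22 SD in the low and full groups illustrates correlations of 0.3 to 0.5; it is not an estimate for this trial.

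A reader might infer that the trial's main result is compromised. The documents do not support that: the primary analysis is the one-year ANCOVA under an intention-to-treat heading, and this clause does not touch it. No sample size or data collection is affected. The error is of moderate severity, in a supporting analysis.

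**What to change.** Replace the clause so that the model has fixed effects for randomised arm, visit (4, 8 and 12 months, categorical) and arm-by-visit, adjusted for baseline CORE-OM and the randomisation strata of section 7.2, with within-woman correlation. Judge stability by the arm-by-visit interaction and the three arm contrasts with their confidence intervals.

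Remove number of sessions from this model and report it in a separate, exploratory analysis. If an effect of receiving the intervention is wanted, a complier-average causal effect analysis is an option. It needs a binary compliance threshold defined in advance and its assumptions stated, because a single binary instrument does not identify effects at separate session levels without further assumptions.

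The cost is one sentence in section 8 and no new data. It is best done before outcome data by arm are seen.

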7.4 Quantitative measures

7.4.1 Mental health measures

- CORE-OM: 34-item self-completed measure of psychological distress that provides a mean overall score (range 0–4) and four domain scores (well-being, problems, functioning and risk). This acceptable, standardised, valid and reliable outcome measure, with sensitivity to change, and UK normative data, was designed to assess efficacy and effectiveness across multiple disciplines offering psychological therapies.24
- PHQ-9
- GAD-7
- Sheehan’s (1986) Post-Traumatic Stress Symptom Questionnaire

The primary outcome of the trial will be a mental health measure, the CORE-OM, for which we already have pilot data in relation to the intervention. To detect a reduction of 0.4 SD on the CORE with a power of 80% at a 5% significance level would require 250 participants in the trial.

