7.4.2 Abuse measures (baseline, 4 month, 8 month and 12 month follow up)

- Composite Abuse Scale (CAS): 30 item self-completed measure of partner abuse with good acceptability and reliability, with some evidence of criterion and external validity. 25 Measures partner lifetime and past 12 month partner abuse (can be adapted for more recent abuse)
- Child abuse measure (three questions)

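### Secondary outcomes are adjusted for baseline CORE-OM instead of their own baseline values, which loses precision and only partly corrects chance baseline imbalance

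*Protocol*

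**What the plan says.** The primary outcome is CORE-OM (section 7.4.1: "The primary outcome of the trial will be a mental health measure, the CORE-OM"). The other outcome scales are therefore secondary: PHQ-9, GAD-7, the post-traumatic stress questionnaire, the Composite Abuse Scale (CAS), SF-12 and EQ-5D.

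Section 8 specifies for the primary outcome: "Analysis of covariance with the one year CORE-OM score as the dependent variable, adjusted for baseline CORE-OM score and the minimisation variables". The mixed model for the repeated CORE-OM scores also adjusts for baseline CORE-OM. For binary and continuous secondary outcomes the same section specifies "logistic regression and analysis of covariance, respectively, adjusted for baseline CORE-OM scores and minimisation variables". Nowhere does the protocol name a secondary outcome's own baseline as a covariate.

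On data collection, item 4.2.3 of section 4 reads "To administer baseline and 4 monthly follow up measures for 12 months from recruitment", without singling out any scale. The heading of section 7.4.2 is explicit for abuse: "Abuse measures (baseline, 4 month, 8 month and 12 month follow up").

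**The concern.** A scale's own baseline usually predicts its follow-up value better than the baseline of another scale does. The primary analysis follows that principle. The secondary rule does not, and no reason is given. It looks as though the covariate phrase for CORE-OM was carried over to every other outcome.

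This is not a detail left open for an analysis plan, because the protocol names the covariates. Followed literally, the rule gives wider confidence intervals for continuous secondary outcomes than the planned data allow. It also leaves in the estimate part of any chance baseline difference on the scale being analysed. The loss should be greatest where CORE-OM is a poor stand-in, and abuse is the plausible example. It also reaches the quality-of-life scales, and quality of life is named in the first aim.

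**Working it through.** **The protocol's own figure.** No sample size or power is stated for any secondary outcome, so there is no figure on this point to reproduce. The only one is for CORE-OM (section 7.4.1): "To detect a reduction of 0.4 SD on the CORE with a power of 80% at a 5% significance level". The total given there is 250. With a two-sided test, 2 × (1.960 + 0.842)² / 0.4² = 98.1, so 99 per arm and 198 in total. The stated 250 is approached with about 20% loss to follow-up (198 / 0.8 = 247.5, so 248), a rate the protocol does not give. That is a separate matter. Only the 125 women per arm are used below.

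**Inputs.** From the protocol: 125 per arm, 1:1 allocation. Assumed, because the protocol gives no correlations: ρ_own, between an outcome and its own baseline, 0.4 to 0.7; ρ_core, between the outcome and baseline CORE-OM, 0 to 0.5 and always below ρ_own.

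**Precision, continuous outcomes.** The residual variance in analysis of covariance is proportional to 1 − ρ². The variance under the stated rule, relative to own-baseline adjustment, is

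(1 − ρ_core²) / (1 − ρ_own²).

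Dividing 250 by this ratio gives the number of women who would provide the same precision with own-baseline adjustment.

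| ρ_own | ρ_core | Calculation | Ratio | 250 women are worth about |
|---|---|---|---|---|
| 0.4 | 0.3 | 0.91 / 0.84 | 1.08 | 231 |
| 0.5 | 0.4 | 0.84 / 0.75 | 1.12 | 223 |
| 0.5 | 0.35 | 0.8775 / 0.75 | 1.17 | 214 |
| 0.5 | 0.1 | 0.99 / 0.75 | 1.32 | 189 |
| 0.6 | 0.3 | 0.91 / 0.64 | 1.42 | 176 |
| 0.6 | 0.2 | 0.96 / 0.64 | 1.50 | 167 |
| 0.7 | 0 | 1.00 / 0.51 | 1.96 | 128 |

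The first and last rows are the extremes of the assumed range. As an illustration in power, take a true difference of 0.3 SD with ρ_own = 0.6 and ρ_core = 0.3:

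- Stated rule: standard error √(2 × 0.91 / 125) = 0.121, power 70%.
- Own baseline: standard error √(2 × 0.64 / 125) = 0.101, power 84%.

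**Chance imbalance.** With 125 per arm, the SD of a chance baseline difference is √(2 / 125) = 0.126 SD, so its 95% range is ±0.25 SD. Let r be the assumed correlation between the two baselines. After adjustment for CORE-OM alone, the shift left in the estimate at the 95% limit is

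[(ρ_own − r × ρ_core) / (1 − r²)] × 0.248 × √(1 − r²).

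- ρ_own 0.5, ρ_core 0.4, r 0.7: 0.431 × 0.177 = 0.08 SD. With no baseline adjustment: 0.5 × 0.248 = 0.12 SD.
- ρ_own 0.7, ρ_core 0.3, r 0.5: 0.733 × 0.215 = 0.16 SD. With no baseline adjustment: 0.7 × 0.248 = 0.17 SD.

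The CORE-OM covariate removes about a third of the shift in the first case and about a tenth in the second. The imbalance is reduced, not eliminated.

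**Logistic models.** The variance ratio does not carry over. Adding a prognostic covariate changes the conditional odds ratio being estimated and does not shrink its standard error in this way. The benefit there is in power.

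**The case against.** The strongest reply is that nothing here is invalid. Randomisation keeps the linear-model estimates unbiased on average and the type I error controlled, whichever baseline covariate is used. The primary analysis is unaffected, and the protocol claims no power for any secondary outcome. All of this stands: the point is about efficiency and conditional accuracy.

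A reader might infer that chance imbalance goes wholly uncorrected. The protocol does not support that. CORE-OM covers well-being, problems, functioning and risk (section 7.4.1), so adjusting for it should absorb part of an imbalance in related scales such as PHQ-9 or GAD-7.

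A reader might also extend the point to the cost per QALY, since QALYs are built from EQ-5D. The cost-effectiveness bullet in section 8 is separate and states no covariates. The quoted rule does not govern it, and its silence may be filled by an analysis plan that is not shown.

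Three further cautions hold. The size rests on assumed correlations and can be small for scales close to CORE-OM. The abuse scale is a less certain example than it seems: section 7.4.2 offers lifetime and 12-month versions and allows a shorter recall period, so baseline and follow-up may cover different windows and the own-baseline correlation may be modest. Finally, baseline collection of the non-abuse scales rests on the general statement in item 4.2.3. That reading is reasonable, but it is not spelled out scale by scale.

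None of this gives a reason to prefer CORE-OM as the sole baseline score in the model.

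**Conclusion.** The point holds as one of efficiency. The stated covariate rule is valid on average but inferior to the one the protocol uses for its primary outcome, and the better rule needs only data already planned. For continuous secondary outcomes the variance is about 8% to 96% larger than necessary over the assumed correlations. A chance imbalance at its 95% limit could leave roughly 0.08 to 0.16 SD in the estimate. These sizes assume that each scale predicts itself better than baseline CORE-OM does, and that all 125 women per arm are analysed. The direction is secure wherever the first assumption holds; the size is not known from the protocol. The finding does not extend to the primary analysis or the QALY comparison.

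**What to change.** In section 8, replace the covariate phrase for secondary outcomes with: *adjusted for the baseline value of the same outcome where measured, and the variables used in the randomisation*. Baseline CORE-OM may stay as an optional additional covariate, provided that this is decided in advance for each outcome. It would help to confirm in section 7.4 that every secondary scale is taken at baseline, and to state the CAS recall period at each visit.

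The cost is one phrase, with no new data and no change to sample size or conduct. It should be settled before outcome data are examined, so that the choice of covariates cannot be influenced by the results.
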